## Abstract

**Background:**

Disproportionate uptake of and access to maternal and child health services remain significant challenges across and within countries. Differing geographic, economic, environmental, and social factors contribute to varying degrees of vulnerabilities among individuals, which manifest as disparities in maternal and newborn health outcomes. Designing solutions according to need is vital to improve maternal and child health outcomes. In this paper, we describe our study protocol on developing and evaluating the effectiveness of human-centered design (HCD) solutions to improve maternal health service uptake among vulnerable pregnant women in rural areas of Ethiopia.

**Methods:**

The study has two distinct phases. In Phase 1, HCD solutions were developed through co-design workshops with vulnerable pregnant women and key stakeholders. Final solutions included home visit education, audio programs promoting couple discussion, and print materials, implemented in collaboration with community health workers and health officers. A community-based, quasi-experimental, mixed-method study design was used to assess differences between intervention and control arms. A panel sample was enrolled after screening for pregnancy and vulnerability level and surveyed at baseline and midline in Phase 1. Phase 2 adopts an identical design approach with a focus on refining Phase 1 solutions. Newly recruited pregnant women will receive refined solutions for six months, which will be evaluated using post-only end-line surveys and in-depth interviews.

**Conclusions and Implications:**

Our sequential approach to evaluating initial solutions, which in turn will inform the enhancement of solutions, will provide practical insights into how solutions are accepted among vulnerable women and how they can be better integrated into women’s lives and health systems. This will inform equity-focused practice and policies targeting populations experiencing greater barriers to accessing care and provide insights into system strengthening in rural areas. Our findings will be disseminated to the Ethiopian Ministry of Health and its partners to inform large-scale implementation at the national level.

## Introduction

Reducing maternal mortality ratio has been one of the major priorities on the global health agenda. With the launch of the Sustainable Development Goals in 2015, the World Health Organization (WHO) and partners reached a consensus on endorsing Target 3.1 that aims to reduce the global MMR to less than 70 per 100,000 livebirths by 2030. The target has shown a steady progress with its 34.3% reduction between 2000 and 2020
^
1
^. However, such aggregated outcomes in health indicators often obscure disparities across countries and within sub-regions.

Ethiopia has shown steady improvements in many maternal and child health indicators over the past two decades. In 2000, the maternal mortality ratio was 871 deaths per 100,000 livebirths, which declined to 412 in 2016
^
2
^. Between 2005 and 2019, under-5 mortality also decreased by 52%
^
3
^. Despite this substantial progress, Ethiopia faces persistent health challenges. The maternal mortality ratio in-country accounts for 3.6% of global maternal mortalities
^
4
^. Twenty-five percent of female deaths from the 2016 data were found to be from pregnancy-related causes
^
2
^, and the neonatal mortality rate also increased by four points per 1,000 livebirths between 2016 and 2019
^
3
^.

To achieve faster and more equitable improvements in maternal and child health outcomes, the government of Ethiopia has implemented a three-tiered health system with an intensive Health Extension Program, which takes a community-based approach to improving health knowledge, health-related skills, and access to primary healthcare
^
5
^. In addition, the Health System Transformation Plan (HSTP-II) is being implemented from 2020 to 2025 with an overall objective to improve the population’s health status by accelerating progress towards universal health coverage, protecting populations during health emergencies, reducing home delivery across woredas (districts), and improving health system responsiveness to the needs of target populations and communities
^
6
^. The HSTP-II has a target to reduce the maternal mortality ratio to 279 per 100,000 live births and under-5 and neonatal mortalities to 44 and 21 per 1,000 live births, respectively
^
6
^. Under these national goals, providing pregnant women with essential maternal health services, including institutional delivery (i.e., childbirth in health facilities attended by skilled birth attendants), antenatal care (ANC), and iron and folic acid supplementation, has been a key strategy for optimizing maternal and child health outcomes in Ethiopia. These maternal health services can significantly reduce the risk of maternal, perinatal and neonatal mortality in low- and middle-income countries and alleviate health disparities worldwide
^
7–
9
^.

Nevertheless, there remains an urgent need to address disproportionate uptake of and access to maternal health services in Ethiopia. Taking institutional delivery coverage as an example, women’s use of health facilities for childbirth greatly varies by region and sociodemographic characteristics. With the national average being approximately 48%, the percentage of institutional delivery use ranges from 23.3% in Somali Region to 94.8% in Addis Ababa, the capital city
^
3
^. Also, 79% of women in the lowest wealth quintile delivered a baby at home; the corresponding figure for women in the highest wealth quintile was 14%. Parity is also associated with home delivery: women having six or more births are more likely to deliver at home, compared to those delivering for the first time.

Prior evidence suggests that women’s use of maternal health services is shaped by multiple factors at the socio-ecological continuum. Barriers to maternal health service uptake among pregnant women reside at multiple levels, including at the individual level (having poor knowledge of obstetric complications and danger signs, low risk perceptions, high parity, and no birth preparedness plans)
^
10–
12
^, social level (social and gender norms, support from family, decision-making power)
^
11,
13,
14
^, cultural level (respect for elders, perception about pregnancy-related matters as women’s privacy, relationship with traditional birth attendants in the community)
^
3,
15–
17
^, structural level (distance to health facilities, transportation and road infrastructure, costs for traveling, delivery cost)
^
11,
15,
18
^, and those that are service-related (lack of services that respect women’s privacy and preferences, disrespectful treatment by health workers, and staff and medical supply shortages)
^
10,
15,
19,
20
^.

Understanding vulnerabilities of key target populations has important implications for developing and implementing tailored programs and policies
^
21
^. Nevertheless, less attention has been paid to how vulnerability is defined, conceptualized and operationalized in the realm of maternal health service coverage
^
22
^. Indeed, despite remarkable improvements in disease-focused service coverage, global health programs have been highlighted as neglecting inequity by not reaching the most disadvantaged population, straining weak local health systems, and distorting local health priorities and agendas
^
23,
24
^. Our project is based on the assumption that accurate and comprehensive assessment of vulnerability in maternal service uptake can help identify vulnerable pregnant women with the lowest likelihood of accessing necessary health services, which will subsequently help generate evidence and provide guidance on effective policies and interventions. Therefore, identifying the most vulnerable pregnant women and engaging them in program development would enhance the applicability, viability, and effectiveness of an intervention. Adopting user-oriented strategies, our study attempts to render vulnerable pregnant women an opportunity to take ownership of their problems and participate in generating solutions with the study team to cater to their unique needs, challenges, and hopes.

Given the complex interplay of factors which prevent or hinder access to maternal health services, and with special attention to the social and economic factors which underpin vulnerability in this context, we chose to adopt a human-centered design (HCD) approach in the development of the solutions. Prior interventions effectively developed HCD-based health solutions, taking account of multiple factors, including decision-making power, gender roles, and social norms
^
25,
26
^. HCD leverages creative thinking through an iterative process and has proven to be a meaningful tool in program and solution design
^
27,
28
^. HCD can offer a novel approach to solution design through putting key stakeholders, in this case pregnant women and the network of providers and volunteers who offer care during pregnancy, at the center of the process to find solutions that are most relevant to their daily lives and circumstances. Further, the iterative nature of HCD allows for the refinement of solutions along multiple axes, including feasibility, sustainability, and ability to be enmeshed in pre-existing health systems.

Furthermore, we argue for the need for conducting implementation research, given that determining
*true* program effectiveness necessitates evidence on how an intervention fits in “real world” settings beyond a controlled study environment. Implementation research is distinguished from monitoring or process evaluation efforts due to its focused goals to explore 1) a program’s likelihood of being adopted and scaled up in real-world settings, 2) contextual factors that may facilitate or hinder implementation, 3) implementation strategies (rather than intervention strategies), 4) and the engagement of stakeholders to achieve successful implementation
^
25
^. Well-designed implementation research provides an insight into whether an intervention would likely be integrated into its target environment, and more broadly, into health systems beyond study duration and scope. Implementation research also generates evidence that helps policy makers and implementers foresee challenges, contributing to saving costs and resources for future programs. Although there is no scientific consensus on what elements and principles are necessary for conducting implementation research, the WHO guide
^
26
^ encourages researchers to outline implementation research questions, use a framework that describes implementation research outcomes, and select a study design and methods that are most pertinent to understand how implementation occurs in a given context.

### Study objectives

The objective of this study is to develop and evaluate the effectiveness of an HCD intervention package through a two-phased sequential study design. Our objective tailored to intervention development is to co-design solutions with vulnerable pregnant women and key stakeholders to improve maternal health service (institutional delivery and ANC) uptake in rural Oromia region in Ethiopia based on 5-step design processes. In Phase 1, HCD solutions (home visit education, audio programs, and print materials) were finalized in January 2024 and implemented until May 2024. Our objective in Phase 2 is to refine the solutions to optimize scalability and ownership in the health system, in turn to ensure service uptake among pregnant women. Our evaluation objectives across the two phases are:

1.To assess whether changes in institutional delivery and ANC visits among women in the intervention arm are significantly greater than corresponding changes in the control arm.2.To explore how social and behavioral factors, including social norms, gender norms, women’s empowerment, and spousal dynamics, are associated with maternal health service uptake.3.To understand the extent to which the intervention meets key implementation research outcomes, including fidelity, acceptability, feasibility, scalability, and sustainability, among pregnant women and health workers in the intervention arm.

## Methods

### Study setting

Administratively, Ethiopia is divided into 12 regions and two administrative cities, with regions further subdivided into zones, woredas, and kebeles (the lowest administrative unit), as described in
Figure 1. Enumeration areas are created by the Ethiopian Statistical Services for the purposes of population and housing census-taking to serve as clusters that typically contain about 750 to 1000 people, with each kebele possibly containing multiple enumeration areas.

**Figure 1. f1:**
[figure not shown]
Administration and health system structure in Ethiopia, adapted from the Federal Ministry of Health (FMOH).

Ethiopia's health system consists of three tiers: the primary tier includes one primary hospital, five health centers, and 25 health posts serving about 100,000 people; the secondary tier comprises general hospitals serving 1 to 1.5 million people; and the tertiary tier includes specialized hospitals serving 3.5 to 5 million people.

Our study sites are in Oromia, the most populous region in Ethiopia. Within this region, Siraro and Shalla woredas were selected as intervention arms, and Gera and Shebe woredas as control arms. The study sites were not randomly selected due to the on-going security issues in Ethiopia. The distance of woredas from major regional towns, maternal and child health service utilization (obtained from the national Health Management Information System data), and major livelihoods of the target study population were taken into consideration in the selection of intervention and control woredas. Two woredas (one nearby and one remote from towns) with similar health service uptake and predominantly agricultural livelihoods were assigned as the intervention group. The same strategies were used to select the control woredas. 

### Study design

A community-based quasi-experimental study design was chosen to assess differences in key variables between the intervention and control arms. We chose a quasi-experimental design for several reasons. We lacked information about clear randomization unit given the characteristics of individuals or clusters (woredas), and it was likely that many woredas in Oromia region are not homogenous towards our outcomes of interest. Another reason was due to resource constraints, as we did not have a sufficient number of woredas in our study to conduct a pure randomized trial design. The study included two waves of data collection from a panel of recruited pregnant women at Phase 1. We attempt to leverage Phase 1 findings to inform the development of study tools and identify factors affecting implementation to provide insights into the improvement our intervention at Phase 2. This study is registered at ClinicalTrial.gov (NCT05907720).

In Phase 1, we conducted the baseline survey with 470 pregnant women enrolled in intervention and control arms in January 2024. After the baseline survey, we implemented a set of HCD prototype solutions in the intervention arm only, keeping the usual standard of care intact in the control arm. After the 4-month period of HCD solution implementation, we conducted the midline survey among the same women in the panel from both the intervention and control arms. In the midline survey, we interviewed 453 pregnant women, with 17 pregnant women lost to follow-up. The midline assessment also included in-depth interviews with purposively selected pregnant women from the panel and health workers who engaged in implementation.

In Phase 2, we will conduct a post-only study with a new sample of vulnerable pregnant women who will be recruited after the implementation of refined HCD solutions. Since the focus is on enhancing implementation feasibility, scalability, and health system ownership of Phase 1 solutions, which have already shown significant improvements in institutional delivery, we believe a post-only assessment is sufficient to observe consistent effectiveness. 

We will compare outcomes between the intervention and control arms at end-line, and the end-line findings will also be compared with the baseline to identify whether refined solutions bring greater impact than our initial solutions did in Phase 1. Thus, our overall study design includes three waves of data points: baseline and midline assessments in Phase 1 and end-line assessment in Phase 2. The study design is further described in
Figure 2.

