### Recruitment

After obtaining a list of all interested women from health extension workers and health development armies, data collectors visit the women in person to screen their pregnancy status and vulnerability level to assess their eligibility. With the woman’s verbal consent, the data collector administers the pregnancy screening tool to identify her pregnancy status. Only women at 5+ months of pregnancy and aged 15–49 are considered eligible. If eligible, she is screened for her vulnerability level, assessed through the vulnerability screening tool. Those considered to be moderately to highly vulnerable are eligible and entered into the sampling frame. Women who score at least 9 out of the maximum 20 vulnerability screening questions will be identified as a study participant. All responses to the screening questions will be entered into the data collectors’ mobile phone application that automatically determines pregnant women’s eligibility during the visit. 

All eligible women are entered into our sampling frame. After listing eligible pregnant women, we aim to recruit approximately three women per enumeration area to achieve our target sample size. If an enumeration area has five or fewer eligible women, they are all contacted for recruitment. If there are more pregnant women than the minimum required number of pregnant women, we randomly select the required number. If a woman is not interested or available for participation, we contact the next randomly selected woman for recruitment. Recruitment continues until our sample size is reached, expanding to other enumeration areas if necessary. Recruitment in Phase 1 was completed in this way, and Phase 2 recruitment will follow this procedure.

For the qualitative assessment, recently delivered women who receive our intervention and health workers in the intervention sites are purposively recruited. Purposive selection of the sample allows us to understand the experiences of engaging in our implementation process among diverse individuals. For women, the selection criteria include: 1) residing in Siraro and Shalla woredas, 2) being exposed to the HCD solutions during their last pregnancy, and 3) having delivered after receiving the solutions. To further obtain diverse and in-depth experiences among our sample, we prioritize recruiting women who are in earlier gestational ages (5

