### Data collection and measurement

**
*Survey interview*.** All participants from Phases 1 and 2 undergo a one-on-one survey interview to assess sociodemographic information, psychological factors, social and structural factors, and maternal health service utilization. A structured interview is administered by a local data collector in the local language. The survey captures the self-reported place of the most recent childbirth along with uptake and frequency of ANC visits during the most recent pregnancy. Secondary outcomes include knowledge, attitudes, and perceptions about maternal health service utilization, social norms, gender norms, spousal dynamics, decision-making, and community and structural factors. Midline (post-intervention in Phase 1) and end-line (post-intervention in Phase 2) assessments additionally include questions measuring program exposure.

**
*Qualitative interview*.** Purposively selected women from the study participants (n=20) along with health workers (n=32) engaged in the program participate in an in-depth interview. Given the 4-month duration of program implementation among pregnant women in their 5
^th^ or higher months of pregnancy, interviews are administered to recently delivered women inquiring about their perceived effects of the intervention on the place of childbirth and ANC uptake during pregnancy. Additionally, the interview guides for women and health workers contain questions around key implementation research outcomes, including acceptability and feasibility, to identify any similarities and differences arising across different types of interview participants.

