### Intervention

**
*HCD workshop procedure*.** In Phase 1, prior to the HCD process, an extensive desk review and secondary data analysis were conducted to identify key drivers of vulnerability affecting uptakes of maternal and child health services (ANC and institutional delivery). Vulnerability driving factors, such as women's illiteracy, distance from health facilities, high parity, decision-making power, exposure to media, and lack of household assets were identified as major barriers to maternal health service use. Based on these factors, a vulnerability screening tool was developed to identify the target population of rural vulnerable pregnant women. Couples who met three or more of the vulnerability criteria among those driving factors (e.g., living over 30 minutes from a health facility, being illiterate, having poor housing conditions, and lacking a mobile phone) were identified. From a desk review and evidence synthesis of secondary data, two initial design challenges focusing on ANC and institutional delivery were prioritized: 1) reimagining how to support pregnant women to attend ANC, and 2) reimagining how to support pregnant women to deliver in a health center. Then, an iterative five-phase design thinking process was implemented, including empathy, define, ideate, prototype, and testing that provides a flexible framework for co-creating solutions with community members and heath care stakeholders. 

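### The protocol gives incompatible accounts of when Phase 2 women are enrolled and whether they are pregnant or delivered; read literally, two of them miss the birth under study and select women after exposure

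*Protocol article*

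**What the plan says.** The Protocol article describes Phase 2 enrolment in four places.

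- **Abstract, Methods:** "Newly recruited pregnant women will receive refined solutions for six months, which will be evaluated using post-only end-line surveys". Recruitment comes first, then exposure, then the survey.
- **Study design:** the post-only study uses "a new sample of vulnerable pregnant women who will be recruited after the implementation of refined HCD solutions". Implementation comes first, and the recruits are still called pregnant.
- **Recruitment:** "Only women at 5+ months of pregnancy and aged 15–49 are considered eligible". The process starts "After obtaining a list of all interested women from health extension workers and health development armies", the vulnerability tool is then applied, and "Recruitment in Phase 1 was completed in this way, and Phase 2 recruitment will follow this procedure".
- **Sample, Table 1:** a separate row for midline and end-line covers recently delivered women. For Phase 2 it admits those who received the solutions and excludes those who were not exposed. No exception is stated for the control arm.

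On the outcome, Data collection and measurement says "The survey captures the self-reported place of the most recent childbirth", together with ANC in the most recent pregnancy.

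**The concern.** Phase 2 has no baseline of its own. Its main evidence is a comparison of arms at end-line, in woredas that were not chosen at random. When women enter, and in what state, therefore decides what that comparison means. Two things are at stake.

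1. **The birth that is counted.** A woman who is five or more months pregnant when she is recruited and surveyed has not yet had the birth that the programme could influence. Her latest birth is an earlier one, or she has none.
2. **Who is counted.** In Phase 1, enrolment and the baseline survey (January 2024) came before implementation (February to May 2024), so neither the worker-supplied list nor the vulnerability score could be affected by the solutions. Run after implementation, both could be, and only in the intervention arm.

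**Working it through.** **Step 1. The accounts side by side**

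| Place | Order | Status when enrolled | Can a control woman qualify? |
|---|---|---|---|
| Abstract, Methods | enrol, expose, survey | pregnant | not addressed |
| Study design | implement, then enrol | pregnant | yes |
| Recruitment | as in Phase 1 | 5+ months pregnant | yes |
| Table 1, delivered row | expose, then enrol | recently delivered | not on the literal wording |

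No sentence reconciles them. The qualitative part of Recruitment treats recruitment as preceding the intervention and applies the same sampling approach at end-line. That fits the Abstract's order.

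**Step 2. Which orders yield the birth under study?** Assume term at nine months. A woman enrolled at month 5 or later delivers within about 9 − 5 = 4 months.

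- Enrolled before a six-month programme and surveyed at its end: nearly all have delivered the enrolled pregnancy.
- Enrolled pregnant after implementation and surveyed at recruitment: 0% have.
- Recently delivered women, as in Table 1: they have, but entry then depends on exposure.

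**Step 3. The plan's own sample size.** Inputs from Sample size calculation: 9-point difference, 80% power, alpha 0.05 (taken as two-sided), 10% non-response. The 48% reference rate is stated for Phase 1 and assumed to carry over, giving 48% against 57%.

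n = [1.96·√(2·0.525·0.475) + 0.842·√(0.48·0.52 + 0.57·0.43)]² / 0.09² ≈ 482.1, so 483 per arm.

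Allowance: 483 × 1.1 = 531.3, or 483 / 0.9 = 537. The stated 531 reproduces. It presumes that every responder contributes the birth under study.

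**Step 4. Illustration: a share f of about 482 responders per arm has that birth, and only they are analysed**

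| f | women per arm | power |
|---|---|---|
| 1 | 482 | 80% |
| 0.75 | 362 | 68% |
| 0.5 | 241 | 51% |
| 0.25 | 120 | 29% |

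If the other women are kept with an earlier birth, the expected difference shrinks to f × 9 points instead, for example 4.5 points at f = 0.5.

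**Step 5. Illustration: selection after exposure.** Suppose there is no true effect, both arms stand at 48%, and a share m of intervention-arm women is missed, whose facility-delivery rate is r. The spurious difference is

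(0.48 − m·r)/(1 − m) − 0.48 = m(0.48 − r)/(1 − m).

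- m = 0.10, r = 0.20: 0.10 × 0.28 / 0.90 = +3.1 points.
- m = 0.20, r = 0.20: 0.20 × 0.28 / 0.80 = +7.0 points.

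The sign turns on r. If listing misses unengaged women (r below 0.48), the intervention looks better. If screening removes women who responded (r above 0.48), it looks worse. The documents give neither m nor r.

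**Step 6. Is there a route for such selection?** The health development armies who help supply the list made the Phase 1 home visits, with help from the health extension workers (Implementation plan). Among the drivers behind the screening tool, "decision-making power, exposure to media, and lack of household assets were identified as major barriers to maternal health service use". The solutions are audio programmes and couple discussion meant to shift social and gender norms, so some drivers could move with exposure.

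**The case against.** Several stronger readings are tempting, and the documents do not carry them.

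- **That Phase 2 will have no births under study.** The article uses the term pregnant women loosely: Study design says 453 pregnant women were interviewed at midline, four months after a panel that was already at five or more months at baseline. Table 1's delivered row has no gestation rule of its own. The 0% in Step 2 is the literal worst case, not a forecast.
- **That the comparison is inflated by 3 to 7 points.** The shares missed and the 20% rate are assumptions. The screening route runs the other way and is inferred, since the 20 items sit in an appendix not shown. Several named drivers, such as illiteracy, distance and parity, hardly change over months.
- **That six months of solutions is impossible for women enrolled at month 5 or later.** The four months in Phase 1 were a programme period, and six months may be one too.
- **That some fixed share would be undelivered at end-line.** Rolling enrolment over six months with 0 to 5 months left to birth gives 2.5/6 = 42%; with 0 to 4 months left it gives 2/6 = 33%. No section describes rolling enrolment.

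A benign reading also exists: the Abstract may describe programme recipients, and Study design a cross-sectional survey sample drawn afterwards. Recruitment after implementation may also loosely mean after roll-out begins. Figure 2, which might settle the order, is not shown. Table 1's exposure criterion makes sense for the qualitative interviews, which are held only in intervention sites.

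What stands is that the text confirms none of these readings. The survey-after-programme reading in particular still leaves listing and screening after exposure.

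**Conclusion.** The concern holds as an unresolved contradiction about the timing of Phase 2 enrolment and women's status at that point. It is more than a missing detail, because the article states the rule several times and the statements lead to different studies. Following Study design and Recruitment literally, with one post-only survey, would record a birth other than that of the pregnancy the programme could affect, and would list and screen women after exposure in one arm only.

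The resulting bias has no known direction and no size that the documents support. The power and bias figures above are illustrations under stated assumptions (48% in controls, term at nine months, chosen shares). Whether covariate adjustment could deal with such selection is not shown either way. The point needs settling before Phase 2 enrolment, since a wrong order in the field would be hard to undo; by Study status, the Phase 2 design process was still being prepared.

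**What to change.** Reconcile the Abstract, Study design, Table 1 and Recruitment into one rule, applied identically in both arms. Preferably:

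1. List women and screen for pregnancy and vulnerability before the refined solutions reach them, over the same calendar period in both arms. Keep that screening score for eligibility.
2. Survey each woman after the birth of the pregnancy identified at enrolment, and count only that birth and its ANC visits.
3. Remove receipt of the solutions as an eligibility criterion for the survey comparison of arms. It can stay for the qualitative interviews.
4. State whether six months is the programme window or each woman's exposure.

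**Cost.** No added baseline survey is needed, but this is more than a change of wording: 1,062 women must be traced to end-line in an area with security problems. Phase 1 lost 17 of 470 (3.6%). The 10% non-response allowance must then also cover loss to follow-up. If the 10% covers both, a loss like that of Phase 1 could fit within it. If 10% non-response comes on top, 531 × 0.90 × (453/470) ≈ 461 women per arm remain, against the 483 from Step 3.
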